## Methods

### Setting and Population

The study will take place at the Mother-Child Simulation Center at CHU Sainte-Justine, between January and March 2016. CHU Sainte-Justine is a standalone pediatric center that houses a 65 bed level 3 Neonatal Intensive Care Unit (NICU). The simulated setting will be a NICU. The simulation center is equipped with appropriate audio-visual equipment.

Residents enrolled in the General Pediatrics and Neonatal-Perinatal Medicine programs will be the target population for this study. This population is selected because (1) residents are regularly exposed to simulation training during their curriculum, and (2) their clinical reasoning ability improves between the 1^st^ and the 6^th^ year of residency, mainly with increasing clinical exposure through rotations [59]. All postgraduate year (PGY) 1 to 6 residents enrolled in the General Paediatrics and Neonatal-Perinatal Medicine programs at Université de Montréal between May 1 and June 30, 2015 will be eligible for inclusion. There will be no exclusion criteria.

### Ethical Considerations

Each resident will be approached for consent by one of the authors. He/she will be informed that participation or lack of participation in the study will not impact residency training assessment. There will be no financial incentive to participate, and participants will be able to opt out at any moment of the study. The findings of this study will be treated anonymously. The project has been approved by CHU Sainte-Justine’s institutional review board on July 15, 2014.

### Study Design

This is a prospective exploratory nonblinded randomized mixed-methods study. Both quantitative and qualitative research methods will be used simultaneously as to comprehensively explore how clinical reasoning develops through both simulation modalities.

Randomization will be stratified according to two different groups depending on their level of exposure to the NICU: (1) novice residents (PGY1 and 2, exposed to less than 8 weeks to the NICU), and (2) expert residents (PGY3-6, exposed to at least 8 weeks to the NICU). These residents have been respectively exposed to at least 5 or 15 simulation sessions during their residency training. Residents will be randomly (by draw of names) allocated by the primary investigator to group A or group B (Figure 1). Group A will be exposed to the SID approach, whereas group B will be exposed to the classical approach of simulation. Participants will be scheduled to complete the study protocol in 60 minutes. In the first 5 minutes, participants will complete the presimulation questionnaire and receive a brief introduction including a period to get physically familiarized with the mannequin (SimNewB; Stavanger, Norway). In the next 30 minutes, residents will complete the clinical simulation scenario after reading a clinical vignette. At the end of the session, participants will have 5 minutes to complete the postsimulation questionnaire (see Multimedia Appendix 1). The course will end with a 20 minutes semistructured interview.

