#### In-Simulation Clinical Reasoning Assessment

In constructing the simulation scenario and vignette, defined cues will be embedded to stimulate hypothesis generation using System-1 of clinical reasoning. After reading the initial patient presentation in the vignette, residents are asked to submit their diagnostic hypothesis by writing. Then, during the scenario, the participant’s verbalization (which is also stimulated by given cues from the nurse) of diagnosis coming to mind will be audio recorded. Both the written and audio-recorded hypotheses will be compared to the diagnoses generated by an expert panel that will be submitted to the same scenario. For example, the presence of thrombocytopenia during the data confirmation part should lead to verbalization of (1) bacterial infection, (2) viral infection, (3) intrauterine grown retardation, and (4) platelets immunization. The presence of skin lesions during the data confirmation part should lead to verbalization of (1) herpetic infection, (2) bacterial infection, and (3) varicella infection.

Iterative discussions supported by the Clinical Reasoning Assessment Tool during SID have been designed to allow development and exploration of System-2 of clinical reasoning regarding data collection, diagnostic hypotheses generation, new data interpretation, and management plan. In the classical approach, it is hypothesized that System-2 is discussed during the debriefing period after the simulation. Exploration of how both simulation approaches impact on performance of System-2 will be done during the semistructured interviews (see below).

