### Data Analysis

This is an exploratory study that will aid in planning a future larger randomized controlled trial. The target population of residents enrolled in the General Pediatrics and Neonatal-Perinatal Medicine programs represents approximately 50 residents. Based on literature from qualitative research inquiry, the adequate sample size consists of the number of participants at which saturation of data is achieved. This well-described process permits cessation of recruitment when additional data does not bring new properties to unsaturated categories [67]. Different authors agree that saturation is reached after 20 to 25 participants [67,68].

Quantitative data will be analyzed using SPSS 20.0 (IBM SPSS, Chicago, IL). Data will be analyzed using descriptive statistics for all variables. For each Likert-scale type question, a significant cut-off will be pre-established. Comparison of positive versus negative responses will be done with the use of chi-square and Fischer’s exact test for nonparametric variables. Number, nature, and order of diagnostic hypotheses will be compared to the responses of a panel of 10 neonatologists from our hospital. A multivariate analysis will be used to investigate potential effects of graduation year, gender, and prior simulation experience on the residents’ evaluation of their clinical reasoning. Statistical significance will be defined as a probability value of <.05.

Qualitative data will help describe if SID allows better assessment of System-1 and 2 of clinical reasoning compared to the classical approach of simulation. Data from audio-recorded semistructured interviews will be analyzed using NVivo 9.0 software. Analysis will occur as data collection pursues. Recurring themes or distinctive aspects about each student’s response will be noted. These notes will be reviewed and expanded as the research continues until saturation of data. Data will be de-identified so that all participants will remain anonymous. Through content analysis, the information will then be categorized according to the principle of convergence [69]. The research team will use deductive analysis and review of all written transcripts.

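### Matching of diagnostic hypotheses to the expert panel is not masked to arm, although coded lists would allow it; this is the only quantitative outcome that residents do not rate themselves

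*Protocol article*

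**What the plan says.** The Study Design section of the protocol article sets the blinding status for the whole study: "This is a prospective exploratory nonblinded randomized mixed-methods study". The same section has the team know the assignment: "Residents will be randomly (by draw of names) allocated by the primary investigator to group A or group B".

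Two sections describe the outcome at issue. Under In-Simulation Clinical Reasoning Assessment: "Both the written and audio-recorded hypotheses will be compared to the diagnoses generated by an expert panel that will be submitted to the same scenario". Under Data Analysis: "Number, nature, and order of diagnostic hypotheses will be compared to the responses of a panel of 10 neonatologists from our hospital". Neither says who does the matching, by what rules, or whether that person knows the arm.

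The material comes in two forms. The first is written: "After reading the initial patient presentation in the vignette, residents are asked to submit their diagnostic hypothesis by writing". The second is spoken during the scenario; the verbalization "of diagnosis coming to mind will be audio recorded". The Description of the Intervention requires verbalization in both arms, so comparable lists will exist for both.

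**The concern.** Deciding whether a spoken phrase is the same diagnosis as one on the panel's list, and where it falls in the sequence, leaves room for judgement. A general remark about infection, for example, might be credited as bacterial, viral or herpetic. A scorer who knows the arm may be more or less generous in one arm without noticing it.

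This matters because nothing else on the quantitative side is measured from outside the resident. The questionnaires collect self-rated stress, reasoning, improvement, satisfaction and agreement with statements. System-2 performance is explored through interviews. The panel comparison is the one quantitative outcome that can be protected from knowledge of the arm.

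The protocol knows the risk. Its background on assessment tools lists raters' own knowledge, experience and cognitive biases among the known problems of judging reasoning. Yet the limitations in the Discussion name the small sample, the lack of a robust before-and-after assessment and the single scenario, but not unmasked scoring. The study is meant to inform a larger randomized trial, so a biased result would be carried forward.

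**Working it through.** There is no figure in the plan to reproduce. The check has two parts: a reading of the relevant sections, and an illustration of size.

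**Reading**

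1. Blinding: the study is labelled nonblinded, and no masked role is named anywhere in the article.
2. Subjectivity: counting hypotheses leaves little room for judgement. Judging their nature and order against the panel leaves more.
3. Feasibility: the written list needs only a code. Raw audio from the SID arm would reveal the arm through the interruptions, so spoken hypotheses must first be turned into plain ordered lists.
4. Exposure: the written list is made before the scenario starts, and anything voiced before the first stop also precedes the difference in format. Unmasked scoring can still bias these parts, but they cannot carry a true effect of the interruptions.

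**Illustration A: a yes/no match**

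Inputs from Data Analysis: significance at P<.05; about 50 eligible residents, so 50/2 = 25 per arm if all join; saturation expected at 20 to 25 participants, so about 24/2 = 12 per arm. Assumed: equal allocation, a true match rate of 50% in both arms, a two-sided test, and leniency δ toward one arm.

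False-positive rate = Σᵢ Σⱼ Bin(i; n, 0.5) × Bin(j; n, 0.5+δ), summed over all tables with p < 0.05.

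| δ (points) | 25 per arm: chi-square (uncorrected) | 25 per arm: Fisher | 12 per arm: chi-square (uncorrected) | 12 per arm: Fisher |
|---|---|---|---|---|
| 0 | 6.5% | 3.3% | 6.4% | 2.3% |
| 5 | 8.1% | 4.4% | 7.2% | 2.7% |
| 10 | 13.1% | 7.8% | 9.5% | 3.9% |
| 20 | 33.4% | 23.2% | 19.0% | 9.4% |

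**Illustration B: a count of matches**

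Assumed: seven creditable diagnoses per resident, SD 1.5 to 2.0 matches, and 5% to 10% of the seven over-credited in one arm.

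- False difference: 0.05 × 7 = 0.35 to 0.10 × 7 = 0.70 matches.
- SE = SD × √(2/n). At n = 25: 1.5 × 0.283 = 0.42 and 2.0 × 0.283 = 0.57.
- Bias/SE: 0.35/0.566 = 0.62 to 0.70/0.424 = 1.65.
- Two-sided rejection at 1.96: 9.5% to 37.8%.
- At n = 12: SE = 0.61 to 0.82, bias/SE = 0.43 to 1.14, rejection 7.1% to 20.8%.

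The seven is only the sum of the four and three diagnoses that the protocol gives as examples. Bacterial infection is in both lists, and herpes and varicella are themselves viral infections, so this is not a scoring key.

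**The case against.** The strongest reply is that the label is a single word, true of residents and instructors, and that an unmasked scorer is inferred from silence on a matter that a full protocol may settle. Part of this stands: the article does not say that the scorer will know the arm. But it fixes the blinding status of the whole study and makes no exception, which is more than an omitted detail.

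A reader might also infer that bias would favour SID because the team expects SID to do better. The documents do not support that for this outcome. The panel comparison is tied to System-1, and the Discussion expects verbalization in the classical arm to act on System-1 in a similar way. The stated advantage for SID concerns self-assessed progression, System-2 and satisfaction. Aware scoring could therefore push either way, including toward the expected similarity.

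Nor does the sentence "Data will be de-identified so that all participants will remain anonymous" show that lists will be stripped of the resident's name but not of the arm. It stands in the paragraph on interview data and says nothing about hypothesis lists.

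The size can be disputed too. Data Analysis states a comparison of residents with the panel and names no between-arm test for it. Chi-square and Fisher's test are given for positive versus negative responses. The between-arm use follows from the study aim. With Fisher's test at 12 per arm, leniency of up to 10 points leaves the false-positive rate below 5%.

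Finally, masking will be incomplete, because whoever extracts hypotheses from SID audio hears the stops. That stands, and it shapes the fix. The study is also exploratory and disclaims statistical generalizability. This limits the weight of the point but does not remove it.

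**Conclusion.** The concern holds in a limited form. A judgement-based outcome, the only quantitative one that residents do not rate themselves, sits in a study declared nonblinded with no assessor exempted, although masked scoring is practicable. Knowledge of the arm could bias the scores in either direction.

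The size is not known from the documents. The illustrations rest on assumed leniency, match rate or SD, allocation ratio and test. Under them, small leniency matters little at these sample sizes, especially with Fisher's test, while 20 points at 25 per arm raises the false-positive rate by 33.4/6.5 = about 5 times (chi-square) or 23.2/3.3 = about 7 times (Fisher). None of these figures should be cited as the expected error of the trial. The change is inexpensive and should be made before sessions begin; it alters no session, intervention or sample size.

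**What to change.** 1. Fix the panel key and the matching rules before any resident's list is scored.
2. Transcribe verbatim, in order, every diagnosis voiced in the scenario segments. Leave out all stop and debriefing dialogue and any marker of where a stop fell. Extraction must follow written rules and make no decision on what matches.
3. Label each list with a study code only.
4. After all sessions have ended, have an existing team member who ran no session and does not hold the arm key score the lists.
5. Score the written list made after the vignette in the same way. Since it precedes any difference between the arms, it can serve as a baseline.
6. If this is not done, name unmasked scoring as a limitation.

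Interviews, where the arm is obvious, may stay unmasked.

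Cost: clerical time to transcribe scenario audio, because the article plans transcription only for interviews. No new staff are needed. The person extracting the hypotheses stays aware of the arm; verbatim, rule-based extraction limits that influence but does not remove it, mainly for the number of hypotheses.

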**Figure 1 figure1:**
[figure not shown]
Study protocol.

### Intervention

#### Personnel

An instructor experienced with programming, control of the computerized mannequin, and the art of debriefing will be in charge of running the scenario according to the residents’ actions and will conduct the iterative discussions and debriefings. A facilitator will also be present in the simulation room to ensure the flow of the scenario and will provide necessary information about the case upon request from the resident. Standardized health professionals (respiratory therapist and/or a nurse working in the Sainte-Justine hospital NICU) will be present and will portray a specialist from their proper field.

#### Description of the Intervention

The SID approach (Figure 2a) consists of a scenario interrupted at three moments and followed by a short debriefing. According to Kuhn’s steps of the medical reasoning process [60], the session is divided into “data gathering”, “data integration,” and “data confirmation”. Each part consists of two phases. First, the participant is asked to manage a simulated patient based on a real-life and complex case. Complexity, uncertainty and environmental factors such as doctor, patients, and encounter factors [25] are voluntarily embedded. The participant is also asked to verbalize his or her first *intuitive* diagnosis as it comes in mind by System-1 activation. Second, the scenario stops and the instructor questions the participant on his clinical reasoning process at that point in time by System-2 activation. Each interruption must be as short as possible in order to keep the trainee in action, and is ended by a one-sentence reconceptualization of the scenario by the instructor before pursuing the scenario (for the two first stops). Discussions include questions regarding data gathering and the rationale of ordered investigations (first stop), data integration, and how investigation results helped reach a diagnosis (second stop), and finally data confirmation and how the management decisions were reached (third stop). There is neither feedback nor guidance from the instructor during the stops in order to not interfere with the participant’s ongoing clinical reasoning process. These stops are “discussions” and not “debriefings”. A short general debriefing ends the session, and provides feedback on reasoning, procedural skills, and knowledge by highlighting the learnt key messages.

The classical approach (Figure 2b) consists of a scenario with no intervention provided by the instructor until debriefing. As in the SID approach, the participant must verbalize his reasoning process and the diagnostic hypotheses as they come to mind during the scenario. Immediately after the scenario, a facilitated debriefing is performed. This debriefing lasts two to three times the length of the scenario and focuses on the participant’s clinical reasoning skills.

**Figure 2 figure2:**
[figure not shown]
Simulation formats. This figure represents structures of (a) SID and (b) classical approach of simulation, with approximate timing in minutes. (a) A three-time interrupted scenario, with three stops that represent iterative discussions concerning data gathering, data integration, and data confirmation. There should be no guidance by the instructor until the real and short debriefing ending the session. (b) A one-shot scenario followed by a true debriefing conducted by the instructor according to the item checked in the clinical reasoning assessment tool. As a standard debriefing, retroaction from the instructor will be possible.

#### Clinical Reasoning Assessment Tool

The Clinical Reasoning Assessment Tool (Figure 3) aids the instructor to identify proper questions during the iterative discussions (SID approach) and in conducting debriefing (classical approach). The authors of the present study have developed this tool because of the absence of such a tool in the literature. It is based on Graber’s classification of diagnostic errors [2,25], Audétat’s practical guide [61] to assist clinical teachers in detecting clinical reasoning difficulties and follows Kuhn’s steps of the medical reasoning process [60]. The objective of this tool is to help the instructor detect the student’s type of diagnostic errors focusing on his reasoning process, and then to determine appropriate questions to ask the student in order to let him verbalize and possibly self-correct his reasoning process. Three types of environmental factors leading to diagnostic errors may be involved in the reasoning process: nonfault factors (also named patients errors, which are out of the control of the physician), human factors and cognitive factors (also named doctor errors) and system factors (also named encounters errors, due to organizational or institutional flaw). Specific failure in the doctor’s cognitive process may be due to faulty knowledge, faulty recognition of cognitive biases or faulty data gathering (orange squares), data integration (green squares), and data confirmation (blue squares). One or two questions per section are suggested to the instructor to allow for exploration of each type of diagnostic error. Finally, a list of the main cognitive biases according to Croskerry et al [62] is provided and a suggested approach is presented. Once the type of error is identified, the instructor has to find one or two specific questions in order to let the student verbalize (or self-correct) his reasoning mistake.

#### Scenario

In order to stimulate the reasoning process, the chosen topic has to be realistic, and hold a range of differential diagnoses. Investigations should be necessary to precise or refute diagnoses in the absence of specific clinical signs. Uncertainty needs to be deliberately embedded. Management must be complex with controversies concerning treatments. Moreover, a range of environmental factors and events can be added to challenge team members by generating dissonance and failures in order to optimize efficiency of simulated team training and adult learning. The amount of provided information has to be minimal and nonspecific aiming to stimulate additional questions from the participant. Answers to participants’ questions must be standardized and should cover a range of possible differential diagnoses. Finally, procedural and relational skills must be embedded in order to portray as closely as possible the real-life environment.

The general structure of the scenario must follow three parts so it can be performed in a single run-through (for the classical approach) or interrupted (for the SID approach). First, a nonmonitored patient presents with minor symptoms but remains clinically stable. The participant has to check the vital signs, ask the nurse for the history and the results of the physical examination, and order investigations. Second, the patient presents with acute collapse. The participant has to interpret investigation results while managing the acutely ill patient. Third, the participant must present a summary of the situation and a treatment plan to his supervisor while pursuing management of the patient. For the SID approach, the scenario is stopped at two times: (1) after ordering investigations, and (2) after receiving results of the investigations and prior to the call from the supervisor. The last stop occurs at the end of the scenario.

Based on these principles, the chosen scenario consists of an infant with disseminated herpes simplex virus infection presenting with secondary septic shock. A newborn will present with tachycardia and will evolve towards hypoxemia and hypotension, requiring intubation and volume expansion. Laboratory findings will reveal viral sepsis with leucopenia, thrombocytopenia, increased C reactive protein, and elevated liver enzymes. Finally, skin blisters will appear during the transfer of information from the participant to the supervisor and will confirm the diagnosis.

**Figure 3 figure3:**
[figure not shown]
Clinical reasoning assessment tool is a useful tool for detecting diagnostic errors (such as nonfault, human factors, cognitive, and system-related) and clinical reasoning difficulties according to Kuhn classification (data gathering, data integration, and data confirmation). Instructor has to read questions for each category of error or difficulty and compare with the student performance during the simulation session. By checking all sort or errors concerning clinical reasoning, this tool permit to build specific questions for the student (without feedback for SID approach) or to construct his debriefing (with feedback for classical approach of simulation).

